# Rationale and design of a randomised clinical trial for an extended cardiac rehabilitation programme using telemonitoring: the TeleCaRe study

**DOI:** 10.1186/s12872-016-0345-9

**Published:** 2016-09-06

**Keywords:** Cardiac rehabilitation, Telemonitoring and telecoaching, VO2, Cardio respiratory fitness, Leisure time physical activity, Randomised controlled trial

## Abstract

**Background:**

Despite the known positive effects of cardiac rehabilitation and an active lifestyle, evidence is emerging that it is difficult to attain and sustain the minimum recommendations of leisure time physical activity. The long-term benefits are often disappointing due to lack of adherence to the changes in life style. Qualitative research on patients’ perspectives suggests that motivation for lifestyle change tends to diminish around 3 months after the index-event. The time most cardiac rehabilitation programmes end. The aim of the present study is to determine if prolongation of a traditional cardiac rehabilitation programme with additional heart rate based telemonitoring guidance for a period of 6 months results in better long term effects on physical and mental outcomes, care consumption and quality of life than traditional follow-up.

**Methods:**

In this single centre randomised controlled trial 120 patients with an absolute indication for cardiac rehabilitation will be randomised in a 1:1 ratio to an intervention group with 6 months of heart rate based telemonitoring guidance or a control group with traditional follow-up after cardiac rehabilitation. The primary endpoint will be VO2_peak_ after 12 months. Secondary endpoints are VO2_peak_ after 6 months, quality of life, physical-, emotional- and social functioning, cardiac structure, traditional risk profile, compliance to the use of the heart rate belt and smartphone, MACE and care-consumption.

**Discussion:**

The TeleCaRe study will provide insight into the added value of the prolongation of traditional cardiac rehabilitation with 6 months of heart rate based telemonitoring guidance.

**Trial registration:**

Dutch Trial Register: NTR4644 (registered 06/12/14).

## Background

Despite the known positive effects of Cardiac Rehabilitation (CR) and an active lifestyle, evidence is emerging that it is difficult to attain and sustain the minimum recommendations of Leisure Time Physical Activity (LTPA) [1, 2]. The long-term benefits of CR are often disappointing due to lack of adherence to the changes in life style [3, 4].

Cardiovascular diseases (CVD) are the leading cause of death and a major cause of disability and lost productivity in adults worldwide [5]. The aging and growth of the population have offset reduction in cardiovascular mortality in the past decade [6].

Both LTPA and Cardio Respiratory Fitness (CRF) are inversely correlated with mortality [7]. Lee et al. evaluated the long-term effects of changes in CRF on cardiovascular mortality. They observed a significant reduction in cardiovascular mortality of 27 % and 42 %, respectively (compared to those with a loss of CRF) in individuals who had either no change or improvements in CRF. The mean interval between the baseline and last examination being 6.3 years. For every 1-MET (Metabolic Equivalent of Task) increase in CRF over time, all-cause and cardiovascular mortality were reduced by 15 % and 19 %, respectively, showing that even small improvements in CRF can have a substantial effect [8].

Qualitative research on patients’ perspectives suggests that motivation for lifestyle change tends to wane around 3 months after the event, when the initial shock has worn off, and most patients start feeling better [9]. In addition to the already low uptake of CR in the Netherlands median total training duration seems to be less than 3 months [10, 11]. Consolidating lifestyle habits require continued attention and appropriate guidance [3]. The transition of a supervised and structured training programme to a continuation without this guidance could be a possible explanation for the low compliance [12]. A better self-efficacy by telemonitoring could help them to be engaged in and actually perform healthy behaviour (e.g. exercise adherence).

The main aim of the present study is to determine whether prolongation of a traditional CR programme with heart rate based telemonitoring guidance for a period of 6 months results in better long-term effects on physical and mental outcomes, care consumption and quality of life (QOL). In order to see whether patients are able to sustain their CRF and LTPA levels after the telemonitoring intervention of 6 months, this will be followed by a 6-month period without telemonitoring guidance.

The primary objective of the study is to assess whether the addition of 6 months of heart rate based telemonitoring guidance to the traditional CR programme results in a higher peak oxygen uptake (VO_2peak_) than a regular follow-up 12 months after CR. Secondary outcome parameters are: VO_2peak_ at 6 months, cardiac structure and function, QOL, physical (LTPA level), emotional and social functioning, traditional risk profile, compliance to the use of the smartphone, adherence to the minimum recommendations of LTPA, care consumption (hospital admissions, outpatient clinic visits, general practitioner (GP) visits, cardiovascular interventions and lab testing) and Major Adverse Cardiac Events (MACE).

## Methods

### Design

This study is designed as a prospective single centre randomised controlled trial. Patients will be evaluated at baseline (T0), after 26 weeks (T1) and 12 months (T2) after randomisation. Figure 1 provides a flowchart of the study protocol. The study complies with the World Medical Association Declaration of Helsinki on ethics in medical research and is approved by the medical ethics committee of Isala (NL48475.075.14; 14.0334). Clinical Trial Registration: NTR4644.

**Fig. 1 Fig1:**
[figure not shown]
Flowchart, illustrating randomisation and testing at different time points

### Patients

The study will enrol in total 120 patients referred to the CR centre of Isala Zwolle. Patients with a minimal attendance of 80 % in the exercise programme, a signed written informed consent and one of the following indications for CR (acute coronary syndrome (ACS), percutaneous coronary intervention (PCI) or coronary artery bypass grafting (CABG) within 3 months prior to the start of the CR programme) will be included. All patients assessed for eligibility will be registered. Exclusion criteria are a contraindication to CR according to the Dutch national guideline, mental impairment leading to inability to cooperate, severe impaired (musculoskeletal) ability to exercise, signs of cardiac ischemia and/or positive exercise testing on cardiac ischemia, insufficient knowledge of the Dutch language, no access, availability or insufficient knowledge of a computer with internet or an implanted cardiac device (pacemaker, ICD) [13].

### Sample size

Preliminary calculations suggest that for an expected difference in VO_2peak_ of 3.0 ml/kg/min between the control and intervention group with an estimated standard deviation of 4.8 ml/min/kg, assuming 90 % power and 5 % significance level (α = 0.05), a total of 108 patients is needed to detect a beneficial effect of telemonitoring. These numbers are based on a previous study that shows the effects of 52 weeks of CR with combined supervised and unsupervised exercise sessions [14]. Taking into account a 10 % dropout we plan to randomise 60 patients in each group.

### Randomisation

At the end of the regular CR programme, patients meeting the in- and exclusion criteria will be informed and requested to participate. After receiving written informed consent, patients will be randomised in a 1:1 ratio to the intervention group with telemonitoring guidance or the control group with a traditional follow-up programme by means of a computerised allocation system applying an algorithm that prevented the care providers or the investigators from predicting the outcome of the randomisation process. This means that the person, who determines if the patient is eligible, at the time of this decision, is unaware of which group the patient will be allocated to. The patient and care providers are not blinded to the intervention.

### Telemonitoring/coaching

Patients in the intervention group are equipped with a smartphone (Samsung Galaxy Ace GT-s5830i, Korea) and Bluetooth connected heart rate monitor (Zephyr, Annapolis, USA). Therefore the device is able to register training mode, training time and also training intensity. The subjects receive a personal moderate to high intensity heart rate zone based on their Cardio Pulmonary Exercise Test (CPET) at T0 and are free to choose which type of exercise they are going to do. Moderate intensity will be defined as an intensity above their individual first ventilatory threshold [15]. The patients in the intervention group will be advised to exercise at least 30 min a day 5 days a week in the above mentioned training zone. During exercise, type of exercise, heart rate and duration will be registered. Afterwards, patients are requested to score their perceived exertion of training (BORG score). Data will be transferred to a secured website through a secured wireless connection (CE registration NL-CAOO2-2014-32838; ISO 27001). Patients will have access to their individual webpage and their training history on the smartphone. Here they are able to see how much and with which intensity they have exercised. They will be contacted by telephone weekly in the first month, every other week in the second month and from then on every month until T1. During these telephone calls (10 in total) patients receive further advice on how to improve their LTPA level. The nurses discuss the exercise data and use motivational interviewing to motivate and stimulate the patient.

### Traditional follow-up

Traditional follow-up after CR consists of one out-patient visit 3 months after hospitalisation. During this visit medication is checked, information about the diagnosis is given and possible complaints are discussed. If necessary addition testing and extra visits are scheduled.

### Cardio pulmonary exercise testing

Cardiopulmonary exercise testing will be performed every visit in both groups using individualised cycle ergometer ramp protocols on an electro-magnetically braked cycle ergometer (Lode Corrival, Lode, Groningen, the Netherlands). Twelve-lead ECG is recorded continuously and blood pressure is measured every 3 min. Oxygen consumption and CO2 production will be measured breath-by-breath by ventilatory gas exchange (Metalyzer 3b, Cortex Biophysics GmbH, Leipzig, Germany).

All patients start with 1 min of rest, thereafter 2 min of unloaded cycling, an individualised ramp protocol in order to reach VO2_peak_ between 8 and 12 min, 1 min of complete rest to measure Heart Rate Recovery (HRR) and finally a recovery period of 4 min. Patients will be encouraged to exercise until levelling off of VO2 despite an increase in workload and/or to a respiratory exchange ratio >1.10. Afterwards, patients are asked to quantify their rate of perceived exertion according to the original BORG score. Peak VO2 will be determined as the mean value of the final 30 s of exercise. The following criteria will be used to correlate the CPET at different time points: <100 ml increase VO2 in the last minute, RER (Respiratory Exchange Ratio) ≥ 1.10, BORG ≥ 17, HR (Heart Rate) > 85 % predicted.

### Medical history, physical examination and additional testing

Medical history, medication and co-morbidities will be screened every visit. During each visit physical examination length, weight and blood pressure (manual auscultation in seated position) will be measured. Waist and hip circumference will be measured and skinfold thickness will be determined (biceps, triceps, sub-scapular, supra-iliac) to calculate lean body mass [16]. Furthermore resting electrocardiogram (supine position) and lung function test will be executed [17].

### Echocardiography

Echocardiographic parameters for cardiac structure and function will be measured at T0 and T2.

#### Structure

From the 2-dimensional echocardiogram, diameter of the aorta, left atrium, left ventricle at end-diastole (LVED) and at end-systole (LVES), end-diastolic wall thickness of the intraventricular septum (IVS), and left ventricular posterior wall (LVPW) will be measured in the parasternal long-axis view, tracing of the area of the left atrium, and diameter of the vena cava inferior at end expiration will be measured in the subcostal view, respectively.

#### Systolic function

Ejection fraction will be calculated using the formula: (LVEDV–LVESV/LVEDV), where left ventricular end-diastolic volume (LVEDV) and left ventricular end-systolic volume (LVESV) from 2-dimensional echocardiograms in the apical 4-chamber view will be determined using the biplane Simpson rule method.

#### Diastolic function

Standard LV inflow pulsed-wave Doppler measurements at the mitral leaflet tips, including peak flow velocity of the early rapid filling wave (E[−wave]), peak flow velocity of the late filling wave due to atrial contraction (A[−wave]), the E/A ratio,(early deceleration time), and isovolumetric relaxation time will be measured to assess global diastolic function. In addition left atrium inflow pulsed wave velocity Doppler measurements will be obtained, including pulmonary venous flow velocities in both diastole (D) and systole (S), and the S/D ratio. To measure myocardial relaxation, pulsed-wave TDI measurements at the septal and lateral mitral annulus will be obtained.

### Questionnaires

Subjects will be asked to fill in several validated questionnaires to assess general health. This includes QOL (KVL-H), physical functioning (IPAQ-long version), emotional functioning (PHQ-9, HADS) and social functioning (MPSS) [18]. These questionnaires will be completed at baseline and after 6 and 12 months.

### Blood analysis

Venous blood samples will be obtained after an overnight fasting period at baseline, after 6 and 12 months. Total cholesterol, serum triglycerides, high-density lipoprotein, low-density lipoprotein, ApoB, HbA1c and glucose are analysed by the biochemical laboratory using standard procedures for the analyses.

### Adverse events

All adverse events will be registered and serious adverse events (SAE) will also be reported continuously to the Contract Research Organisation (CRO) Diagram. SAE are defined as cardiovascular mortality, all-cause mortality, near sudden cardiac death, ACS, CV intervention/surgery, CV hospital admission and CV emergency visit.

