### Care consumption and MACE

The occurrence of events (cardiovascular mortality, all-cause mortality, near sudden cardiac death, ACS, CV Intervention/surgery, CV hospital admission, CV emergency visits) and consumption of care (admission days, outpatient clinic visits, GP visits, interventions, radiology, nuclear and lab testing) will be collected by a (monthly) telephone call with the participants throughout the study period and patients’ electronic medical files.

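### The closed SAE list leaves out serious events that are neither fatal nor cardiovascular, so they are registered but not classed or reported as serious

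*Protocol article*

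**What the plan says.** Three parts of the protocol article bear on this.

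- **Adverse events** sets the reporting route: "All adverse events will be registered and serious adverse events (SAE) will also be reported continuously to the Contract Research Organisation (CRO) Diagram". It then gives the definition: "SAE are defined as cardiovascular mortality, all-cause mortality, near sudden cardiac death, ACS, CV intervention/surgery, CV hospital admission and CV emergency visit". The list is closed. It has no wording that marks the items as examples and no general criterion of seriousness.
- **Care consumption and MACE** names the events to be collected from telephone calls and medical files: "cardiovascular mortality, all-cause mortality, near sudden cardiac death, ACS, CV Intervention/surgery, CV hospital admission, CV emergency visits". The same sentence also covers "consumption of care (admission days, outpatient clinic visits, GP visits, interventions, radiology, nuclear and lab testing", with no cardiovascular limit on those resource items.
- **Telemonitoring/coaching** describes the exposure in the intervention group. Patients receive a personal heart rate zone of moderate to high intensity, "are free to choose which type of exercise they are going to do", and are "advised to exercise at least 30 min a day 5 days a week in the above mentioned training zone". Guidance is by telephone.

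The Statistics section describes one event analysis, time to MACE by Kaplan-Meier curves and a logrank test. It describes no table or comparison of SAEs.

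**The concern.** In safety reporting, seriousness should reflect what an event does to the patient. Here, except for death, it depends on the organ system involved. A patient who is admitted with a fracture after a fall during training has had a serious event in any ordinary sense, yet under this definition it ranks with a trivial complaint.

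The choice matters more here than in many trials because the intervention is more exercise. If it works as intended, the arms will differ in exercise exposure, and musculoskeletal injury is a plausible harm of that exposure. The SAE list has no place for that class of harm unless it is fatal. At stake are what the CRO sees as the trial runs, and whether a later SAE summary can say anything about safety beyond what the MACE endpoint already says.

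**Working it through.** The plan states no figure on this point, so the check is a comparison of the two lists, followed by applying the rule to example events.

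**Step 1. Compare the lists.** The inputs are the definition under Adverse events and the event list under Care consumption and MACE.

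| Item (paraphrased) | SAE list | Event list | Can it include a non-fatal, non-cardiovascular event? |
|---|---|---|---|
| Cardiovascular death | yes | yes | no |
| Death from any cause | yes | yes | no (fatal by definition) |
| Near sudden cardiac death | yes | yes | no |
| ACS | yes | yes | no |
| CV procedure or operation | yes | yes | no |
| CV admission | yes | yes | no |
| CV emergency attendance | yes | yes | no |

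The lists agree on 7 of 7 items. They differ only in one capital letter and one plural. None of the seven can include an event that is both non-fatal and non-cardiovascular.

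**Step 2. Apply the rule to example events.** These are hypothetical and serve only to show the classification.

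| Event | Registered as adverse event | Admission days in care consumption | SAE, reported continuously to the CRO |
|---|---|---|---|
| ACS during training | yes | yes, if admitted | yes |
| Fatal fall | yes | yes, if admitted | yes, as death from any cause |
| Fracture with admission, survived | yes | yes | no |
| Life-threatening non-cardiac event, survived | yes | yes, if admitted | no |
| Injury with lasting disability, no admission | yes | no | no |

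The gap is the last three rows. In each the event is recorded somewhere, but not as serious.

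**Step 3. What a summary of SAEs could show.** If the event list is taken as the MACE definition, which is the natural reading of its section heading, the set of SAE types equals the set of MACE types. A count of SAEs by arm would then add little to the MACE analysis, and would contain no non-fatal non-cardiovascular harm in either arm.

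**Step 4. What is not touched.** The primary endpoint is peak VO2 at 12 months, and the sample size rests on the difference and standard deviation of that measure. Neither uses the SAE definition.

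**The case against.** The strongest reply is that nothing is lost. All adverse events are registered, admission days, interventions and radiology are collected whatever the cause, and hospital admissions are part of a secondary outcome. This stands. A reader might infer that such events go unrecorded, and the document does not support that: the gap is in classification and reporting route, not in capture. It does not remove the point, because admission days measure resource use, and nothing in the text treats a non-cardiovascular admission as a serious safety event.

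Other stronger readings are also unsupported:

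- *That no non-cardiovascular event can be serious.* Death from any cause is on the list, so a fatal fall is an SAE.
- *That a planned safety comparison will mislead.* The Statistics section states no SAE comparison or table. The consequence applies to any SAE summary that may be made.
- *That the document formally equates SAE with MACE.* The matching list is called events, under a heading that names MACE. Reading it as the MACE definition is an inference, though a natural one. The defect in the SAE definition does not depend on it.
- *That patients train alone, and that injuries will differ by arm.* The text says neither. Patients choose their exercise, wear a heart rate monitor and receive ten calls, and those with severely impaired ability to exercise are excluded. A difference in injuries is plausible, not shown.
- *That the number of affected events can be stated.* An assumed rate of 5-10% among 120 patients would give 0.05 × 120 = 6 to 0.10 × 120 = 12 non-cardiovascular admissions. That rate is not in the document, covers admissions of every cause in both arms, and says nothing about exercise injury.

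It may also be said that an article condenses a fuller protocol. That would answer a missing detail. Here the definition is stated outright, and a general criterion of seriousness elsewhere would contradict it.

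**Conclusion.** The point holds as a misclassification of harms. As written, a non-fatal, non-cardiovascular event cannot be an SAE whatever its consequence, and so does not reach the CRO through continuous reporting. An SAE summary built on this definition could not show serious non-cardiovascular harm by arm.

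Its size in events is unknown. The conclusion rests on reading the list as closed, which is what its wording says. The further remark that an SAE count would largely repeat MACE rests on taking the matching event list as the MACE definition. The primary result is not threatened. The defect concerns safety reporting, and it should be corrected because the correction is cheap.

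**What to change.** Define an SAE by outcome, whatever the organ system: an event that results in death, is life-threatening, leads to hospital admission or prolongs it, or causes lasting disability. Keep the cardiovascular list for MACE, and say explicitly that it is the MACE definition. Reclassify the adverse events already registered under the new rule, and report those that now qualify to the CRO. Tabulate SAEs by arm, with exercise-related injuries as a separate line. If the full protocol already holds a definition by outcome, the article's definition must be reconciled with it.

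The cost is a short amendment, more SAE forms, and work on events already on file. That last part is not negligible: the Preliminary results report 122 patients included against a target of 120, so enrolment appears complete and part of the change must be applied to existing records. It is feasible because all adverse events are registered and the medical files are consulted in any case.

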### Care consumption and MACE

The occurrence of events (cardiovascular mortality, all-cause mortality, near sudden cardiac death, ACS, CV Intervention/surgery, CV hospital admission, CV emergency visits) and consumption of care (admission days, outpatient clinic visits, GP visits, interventions, radiology, nuclear and lab testing) will be collected by a (monthly) telephone call with the participants throughout the study period and patients’ electronic medical files.

